## Abstract

**Background:**

While it is well established that perioperative use of oral nutrition supplement (ONS) improves nutrition status among severely malnourished surgical cancer patients, the evidence requires further substantiation for non-severely malnourished patients with cancer. This protocol paper presents the rationale and design of a randomised controlled trial to evaluate the effectiveness of preoperative as well as an extended 90-day postoperative use of ONS on nutritional and clinical outcomes among patients undergoing elective surgery for breast and colorectal cancer.

**Methods:**

Patients with primary breast and colorectal cancer undergoing elective surgery are recruited from two tertiary hospitals. Eligible patients are assigned into one of the three intervention arms: (i) Group SS will receive ONS in addition to their normal diet up to 14 days preoperatively and postoperatively up to discharge; (ii) Group SS-E will receive ONS in addition to their normal diet up to 14 days preoperatively, postoperatively up to discharge and for an extended 90 days after discharge; and (iii) Group DS will receive ONS in addition to their normal diet postoperatively up to discharge from the hospital. The ONS is a standard formula fortified with lactium to aid in sleep for recovery. The primary endpoints include changes in weight, body mass index (BMI), serum albumin and prealbumin levels, while secondary endpoints are body composition (muscle and fat mass), muscle strength (handgrip strength), energy and protein intake, sleep quality, haemoglobin, inflammatory markers (transferrin, high sensitivity C-reactive protein, interleukin-6), stress marker (saliva cortisol), length of hospital stay and postoperative complication rate.

**Discussion:**

This trial is expected to provide evidence on whether perioperative supplementation in breast and colorectal cancer patients presenting with high BMI and not severely malnourished but undergoing the stress of surgery would be beneficial in terms of nutritional and clinical outcomes.

**Trial registration:**

ClinicalTrial.gov NCT04400552. Registered on 22 May 2020, retrospectively registered

**Supplementary Information:**

The online version contains supplementary material available at 10.1186/s13063-021-05716-5.

## Introduction

### Background and rationale {6a}

The incidence of cancer is on an increasing trend worldwide with colorectal and breast cancers as the leading cause of cancer deaths amounting to 9.2% and 6.6% of total cancer deaths, respectively [1]. About half of the global cancer incidence and mortality are reported in Asian countries [1] and cancer treatment has imposed a tremendous economic burden on low- and middle-income countries such as Malaysia [2]. The management of new cancer cases alone could amount to RM108 million (USD 26 million) per year excluding the costs for therapies, surveillance, and palliative care [2]. Besides, patients may also experience loss of employment and earnings following the diagnosis of cancer [3].

Surgery is the best hope of cure [2] and remains the preferred modality of treatment for cancer [4]. However, the nutrition status of patients undergoing surgery for cancer can impact prognosis. Malnutrition is associated with higher adverse surgical outcomes, higher rate of toxicities during adjuvant therapies, decreased performance status, and worse disease prognosis among surgical cancer patients [5–7]. The prevalence of malnutrition among cancer patients prior to surgery is reported to range between 30 and 60% globally [8–10]. The primary tumour can induce nutritional and metabolic alterations resulting in elevated resting metabolic rate, insulin resistance, increased protein catabolism, and lipolysis which aggravate weight loss [7, 11]. Moreover, the unfavourable effects of the treatment course of surgery such as anorexia, diarrhoea, and small intestinal bacterial overgrowth can further exacerbate patients’ nutritional status [7].

Breast and colorectal cancers are among the most common cancers reported globally with 2 million and 1.8 million new cases diagnosed, respectively [1]. Breast and colorectal cancer patients may not exhibit classical signs and symptoms of malnutrition and are predominantly having an overweight or obese body mass index upon diagnosis [12, 13]. At the same time, being overweight or obese is also one of the known risk factors for the development of breast and colorectal cancers [14–17] and can worsen the treatment outcomes [18, 19].

Although most evidence-based guidelines recommend delaying elective surgery for patients who are malnourished to offer nutritional intervention preoperatively [11, 20], colorectal and breast cancer patients who are predominantly overweight or obese and do not exhibit traditional measures of malnutrition do not commonly receive nutrition care [12, 13]. Most studies defined nutritional status and nutritional outcomes based on the presence of unintentional weight loss and body mass index [21]. There is increasing evidence that the measurement of body composition such as muscle and fat mass could better reflect nutritional intakes, losses, and needs over time [22] and has a more significant impact on the surgical outcomes [6, 23]. Studies showed that following the trajectory of the disease and treatment course, these patients can present with weight loss and sarcopenic obesity characterised by low muscle mass and high fat mass [24]. Significant weight loss could lead to the shortest survival, even after controlling for age, sex, cancer site, stage, and muscle performance [25], and sarcopenic obesity was found to increase mortality among the population treated for cancer [23, 24, 26].

Nutrition intervention has been known to improve nutrition intake and attenuate weight loss [27]; however, lesser studies are reporting the impact of ONS on body composition indices such as muscle and fat mass. It is essential to have a robust nutritional assessment on cancer patients with nutrition risk and to demonstrate if oral nutrition supplementation (ONS) would benefit patients with mild to moderate malnutrition using measurements beyond body weight and BMI.

The optimal duration of oral nutrition supplementation provision to surgical cancer patients is being debated [28]. Across several studies, the duration of preoperative supplementation ranged from 5 days to 4 weeks with an average of 15 days [21]. The reported benefits of ONS are inconsistent even for the same duration of supplementation that might be due to differences in the baseline nutrition status of patients [29, 30]. As for post-operative supplementation, it is also ambiguous if extended supplementation post-surgery would be beneficial. Clinical benefits were observed with supplementation for 2 months after surgery [31] but not with long-term supplementation extending up to 4 months [32]. More data on the duration of supplementation to produce favourable outcomes is needed because this can impact the overall cost of treatment, especially to patients from low- and middle-income countries.

Therefore, this study is designed to address these research gaps by investigating the effect of perioperative ONS supplementation with and without extended supplementation post-operatively on nutrition status and clinical outcomes among patients with breast and colorectal cancers.

### Objectives of the study {7}

The primary objective of this study is to evaluate the impact of perioperative oral nutrition supplementation on nutritional outcomes among patients with primary breast and colorectal cancer and who are mildly malnourished. The secondary objectives are to assess the impact of perioperative oral nutrition supplementation on dietary intakes, body composition, inflammation, and postoperative outcomes in this population.

### Study design {8}

This study is a multi-centre, open-label, multi-arm, parallel-group randomised controlled trial at two tertiary hospitals. This protocol is written in accordance with the Standard Protocol Items: Recommendations for Interventional Trials (SPIRIT) checklist. The schedule of enrolment, interventions, and assessments for the duration of the study is tabulated in Table 1. Patients enrolled in the study are randomised into 3 arms and followed up at baseline, a day prior to surgery, a day prior to discharge, 30 days after surgery, and 90 days after surgery (Fig. 1).

**Table 1 Tab1:**
[figure not shown]
Schedule of enrolment, interventions, and assessments for the duration of the study

**Fig. 1 Fig1:**
[figure not shown]
Study flowchart

## Methods: participants, interventions, and outcomes

### Study setting {9}

This study is conducted at two large tertiary hospitals in Negeri Sembilan (Hospital Tuanku Ja’afar) and in Kuala Lumpur (Hospital Kuala Lumpur) that provide surgical treatments to patients diagnosed with breast and colorectal cancers. The screening, recruitment, and baseline data collection are conducted at the surgical outpatient clinics of the hospitals. The patients are followed up at the surgical wards a day prior to surgery and a day prior to discharge from the hospitals. Upon 30 days and 90 days after surgery, the follow-up data collection is carried out at the surgical outpatient clinics of the hospitals.

### Participants and eligibility criteria {10}

Potential patients are acquired through assessing the registry of surgical clinics and direct referrals from the doctors at the clinics. Patients are eligible if he or she meets the following criteria: male or female from all ethnicity, aged between 25 and 65 years, diagnosed with breast or colorectal cancer and scheduled for elective surgery, BMI not less than 18.0 kg/m^2^, stabilised comorbidities based on the A.S.A Physical Status Classification System Class 1 and 2 [33], and met at least two characteristics of A.N.D/A.S.P.E.N diagnosis of malnutrition, i.e., insufficient energy intake, weight loss, loss of muscle mass, loss of subcutaneous fat, localised or generalised fluid accumulation, and diminished functional status as measured by handgrip strength [34]. Patients who require enteral or parenteral feeding; are currently pregnant or lactating; currently on chemotherapy or radiotherapy; have done total gastrectomy or ileostomy; are diagnosed with metastasised cancer, upper gastrointestinal cancer, terminal diseases, decompensated liver or renal disease, dementia, and the major concurrent metabolic problem such as uncontrolled diabetes; and are currently on regular steroids prescription are excluded. Patients involved in the Enhanced Recovery After Surgery (ERAS) protocol will not be recruited into this study.

### Informed consent {26a}

All invited patients are required to provide written consent after receiving a detailed explanation of the study objectives and risks and benefits of the study (Appendix A). These consents are obtained by the graduate research assistant.

### Additional consent provisions for collection and use of participant data and biological specimens {26b}

The consent of use of patient data and biological specimens has been included in the informed consent in section 26a. No additional consent is required.

### Interventions

#### Explanation for the choice of comparators {6b}

Eligible patients are randomised into one of the three intervention arms: Group SS, Group SS-E, and Group DS. Patients in Group SS will consume the ONS ranging from 5 to 14 days in addition to their normal diet preoperatively and postoperatively up to discharge from the hospital. Patients in Group SS-E will consume the ONS ranging from 5 to 14 days in addition to their normal diet preoperatively, post-operatively up to discharge from the hospital, and for an extended period of 90 days post-operatively. Group DS is the usual care group who will follow their normal diet preoperatively and only consume ONS in addition to their normal diet postoperatively up to discharge from the hospital.

#### Intervention description {11a}

Patients are provided with standard milk based ONS (Appeton Wellness Recovery, Kotra Pharma (M) Sdn Bhd) in which each serving is prepared by adding 4 levelled scoops of powder (55g) into 210ml of lukewarm water. Patients are required to consume 3 servings of the ONS a day which provides additional calories of 750 kcal and 33g of proteins a day. The ONS is also fortified with micronutrients and hydrolysed casein (Lactium®) which has evidence of improving sleep quality [35].

#### Criteria for discontinuing or modifying allocated interventions {11b}

Patients will be withdrawn from the study if they wish to withdraw or experience serious adverse events (SAEs) for any reason.

#### Strategies to improve compliance to interventions {11c}

The compliance to ONS is expressed by the actual amount consumed in grammes divided by expected grammes to be consumed. Patients are given the ONS in cans which are pre-weighed and unconsumed powder is returned and weighed. Patients are also required to record the timing and number of scoops taken daily. Both opened and unused cans are collected from the patients during the succeeding visits. Regular phone calls or text reminders are sent to patients fortnightly to enhance compliance.

#### Relevant concomitant care permitted or prohibited during the trial {11d}

All relevant medical care is permitted.

#### Provisions for post-trial care {30}

There is no provision for post-trial care because patients are under the surgical and dietetics care provided by the hospitals.

### Outcomes of the study {12}

The schedule of enrolment, interventions, and assessments for the study is shown in Table 1. The primary outcomes are body weight, body mass index (BMI), serum albumin, and pre-albumin level. The secondary outcomes include energy and protein intake, muscle and fat mass, handgrip strength, haemoglobin, serum transferrin, high sensitivity C-reactive protein (hs-CRP), interleukin-6 (IL-6), salivary cortisol, sleep quality, length of hospital stay, and postoperative complication rate within 30 and 90 days after surgery. The changes for these parameters will be assessed at a day prior to discharge (V3), 30 days after surgery (V4), and 90 days after surgery (V5) compared to baseline as shown in Table 2.

**Table 2 Tab2:** Outcome parameters’ description

Domain	Specific measurements	Metric and time points for assessment	Method of aggregation
Primary outcomes			
Nutrition status	Body weight, kg	Change from baseline (V1) at1 day prior to discharge (V3); change from 1 day prior to discharge (V3) at 30 days after surgery (V4); change from 1 day prior to discharge (V3) at 90 days after surgery (V5)	Mean
	BMI, kg/m^2^		
	Serum albumin, g/L		
	Serum prealbumin, mg/L		
Secondary outcomes			
Nutrition status	Handgrip strength, kgF	Change from baseline (V1) at 1 day prior to discharge (V3); change from 1 day prior to discharge (V3) at 30 days after surgery (V4); change from 1 day prior to discharge (V3) at 90 days after surgery (V5)	Mean
	Muscle mass, kg		
	Fat mass, kg		
	Serum transferrin, g/L		
	Haemoglobin, g/dL		
Inflammation	High-sensitivity C-reactive Protein (hs-CRP), mg/L		Mean
	Interleukin-6 (IL-6), pg/ml		
	Salivary cortisol, μg/dL		
Dietary intake	Energy intake, kcal/d		Mean
	Protein intake, g/d		
Sleep quality	Pittsburgh Sleep Quality Index (PSQI) score		Median
Postoperative complications	Postoperative complications	Frequency of postoperative complications at discharge (V3), at 30 days after surgery (V4), and 90 days after surgery (V5)	Median
	Length of hospital stay	Number of days of hospitalisation from admission (V1) to 1 day before discharge (V3)	Median

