### Sample size calculation {14}

The sample size required is calculated based on the improvement in serum albumin level. To detect a between-group difference of at least 4g/L of serum albumin level that would cause approximately 25% reduction in morbidity among patients who have serum albumin in the normal range (around 38 g/L) [36], and a standard deviation of 6.5g/L, at 80% power and with a 5% alpha error. A minimum of 23 subjects per group is required. After accounting for a 20% drop-out rate, 28 subjects are required per group and thus a total of 84 subjects will be recruited in the three groups.

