## Assignment of interventions: allocation

### Randomisation {16a}

This is an open-labelled study and randomisation is performed using computer-generated software [37] by personnel not involved in the data collection. Patients are randomised into one of the three intervention arms in the ratio of 1:1:1 without stratification by study sites. The randomisation is done through the block method whereby the block size is either 3, 6, or 9 to minimise predictability and selection bias.

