## Statistical methods

### Statistical methods for primary and secondary outcomes {20a}

Statistical analyses will be performed using the Statistical Package for the Social Science software (SPSS version 26, IBM, USA). The normality of the data will be evaluated using Shapiro-Wilk’s test. Normally distributed data will be expressed as mean and standard deviation. Skewed data will be described using median with interquartile range for skewed data. Categorical data will be expressed in count and percentages. Evaluation of outcomes will be carried out by both intention-to-treat and per-protocol analyses. The primary analysis will take a per protocol approach and the secondary analysis an intention-to-treat (ITT) approach. The per protocol analysis will include patients who fully completed the intervention allocated and attended all visits (‘complete cases’ approach). The primary analysis will employ repeated measures ANOVA (RMANOVA) to assess for time × group interactions. A secondary analysis of difference between groups for continuous variables will be conducted by using analysis of covariance (ANCOVA), controlling for baseline or at discharge values. The ITT approach will include all patients who are randomised to the three groups, irrespective of dropouts. In order to perform RMANOVA using the ITT approach, missing data will be imputed with the last observation carried forward method using the last available data point from the patients. ANCOVA will be restricted to per-protocol basis. *P*-value <0.05 is considered statistically significant for all tests.

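### Four co-equal primary outcomes are each tested at an unadjusted 0.05 with no rule for success, giving about a 14–16% chance of a false-positive primary result on the stated primary analysis

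*Protocol article*

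**What the plan says.** - **Outcomes.** Outcomes of the study {12}: "The primary outcomes are body weight, body mass index (BMI), serum albumin, and pre-albumin level". They have equal rank.
- **Intervals.** Table 2 gives each outcome three changes: baseline (V1) to the day before discharge (V3), then "change from 1 day prior to discharge (V3) at 30 days after surgery (V4); change from 1 day prior to discharge (V3) at 90 days", the last being V5. The text above the table instead describes changes at V3, V4 and V5 relative to baseline.
- **Arms.** Randomisation {16a} sets three arms, 1:1:1.
- **Sizing.** Sample size calculation {14}: "The sample size required is calculated based on the improvement in serum albumin level". It uses one between-group difference of 4 g/L, SD 6.5 g/L, 80% power and 5% alpha, and arrives at 23 per group (28 after drop-out).
- **Tests.** Statistical methods {20a}: "The primary analysis will employ repeated measures ANOVA (RMANOVA) to assess for time × group interactions". Then: "A secondary analysis of difference between groups for continuous variables will be conducted by using analysis of covariance (ANCOVA"), adjusted for baseline or discharge values.
- **Threshold.** The same section says that a P-"value <0.05 is considered statistically significant for all tests".

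**The concern.** With four primary outcomes of equal standing, the same threshold for each and no decision rule, a reader would take any one P value below 0.05 as a positive primary result. The 5% error rate then applies to each test and not to the trial's primary claim.

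Two features make this matter more here. Who will be blinded {17a} says that the trial is open-label and analysed by unblinded investigators, so an advance rule is the main protection against choosing the favourable outcome afterwards. And Anthropometric measurements defines BMI as weight over height squared. In adults aged 25 to 65 height is fixed, so BMI change is weight change divided by a constant for each patient. One weight result could be presented as two primary findings.

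**Working it through.** **1. The plan's own figure.** The sizing covers a single albumin comparison at an undivided 0.05, with nothing set aside for the other three outcomes. The stated 23 per group does not follow from the stated inputs for a two-group comparison: n = 2 × (1.960 + 0.842)² × 6.5² / 4² = 41.5, so 42 per group. A one-sample or paired t test with d = 4/6.5 gives 22.7, so 23. That discrepancy is a separate matter and nothing below depends on it, except that it sets the power available for any adjustment.

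**2. Stated primary analysis: one interaction test per outcome.** For k independent tests at 0.05, the chance of at least one false positive is 1 − 0.95^k.
- k = 4: 1 − 0.95⁴ = 18.5%.
- k = 3 (weight and BMI counted as one): 1 − 0.95³ = 14.3%.

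The outcomes are correlated, so this was also simulated under no treatment effect: 23 per arm, four outcomes, visits V1, V3, V4 and V5. The documents give no correlations. The assumed values were weight–BMI 0.90–0.97, albumin–prealbumin 0.4–0.7, other pairs 0.1–0.5, and between visits 0.5–0.8. The result is about 14–16%; individual settings ran from 13% to 17%. With Holm across the four tests it falls to about 4%.

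**3. Secondary ANCOVA, if every Table 2 interval is tested.** 4 outcomes × 3 intervals = 12 three-arm tests.
- Independence: 1 − 0.95¹² = 46.0%.
- Simulated: about 32–40%.

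**4. Hypothetical: all pairwise arm contrasts as well, unadjusted.** 12 × 3 pairs = 36 tests.
- Independence: 1 − 0.95³⁶ = 84.2%.
- Simulated: about 60–70%.

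The article does not specify these contrasts.

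**5. What a stricter threshold costs.** Power of a two-sided two-sample t test with 4 g/L, SD 6.5 g/L and 23 per arm:

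| Alpha | Power |
|---|---|
| 0.05 | 53% |
| 0.025 | 42% |
| 0.0167 (first Holm step, three outcomes) | 35% |
| 0.0125 (first Holm step, four outcomes) | 31% |

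These are for one comparison of two arms, not for the interaction test, whose power the documents do not allow to be computed.

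**The case against.** **The unseen analysis plan may deal with this.** A journal article leaves much to it, and the post-hoc procedure for arm contrasts is commonly settled there. Adjusted pairwise P values can also be compared with 0.05. This stands for the pairwise layer, where the article is merely silent. It does not stand across the four outcomes, because the article names all four as primary and positively fixes 0.05 for all tests.

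**Arms and intervals do not multiply the primary test.** This is correct. The interaction test is one overall test per outcome, and the intervals multiply only in the ANCOVA, which is labelled secondary. A reader who multiplies four outcomes by three intervals by three pairs might infer that a false-positive primary result is more likely than not. The documents do not support that: the primary analysis gives about 14–16%, and the 60–70% and 84% figures need tests that the article never describes.

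**BMI adds little error if it duplicates weight.** This also stands, and is why the three-test figure of 14.3% is closer than 18.5%. The objection to BMI is double presentation of one result more than extra error.

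**All four might have to be significant.** Under that rule the error would not exceed 5%. But the article states no such rule, and the sizing on albumin alone does not suggest one.

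**Conclusion.** The concern holds in this form: four unranked primary outcomes, one of them sized, all judged at 0.05 with no success rule. If any one result suffices, the chance of at least one false-positive primary result is about 14–16%, roughly three times the nominal level. That rests on assumed correlations, but the independence figures of 14.3% and 18.5% give the same picture. Repeating the repeated measures ANOVA in the per-protocol and intention-to-treat sets adds some further opportunity, not counted here. The 32–40% figure belongs to the secondary analysis and 60–70% to a hypothetical one; neither should be quoted as the error of the stated primary analysis.

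**What to change.** Settle one of these before any analysis. Interim analyses {21b} places all analysis at study completion, so there is time.

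- **Preferred.** Make serum albumin, the sized outcome, the single deciding primary outcome. Test it either by the stated time-by-group interaction or at one named visit with its reference visit given, and reconcile the text (change from baseline) with Table 2 (V4 and V5 measured from V3). Move prealbumin, weight and BMI to secondary. No alpha split across outcomes is needed.
- **Alternative.** Keep albumin, prealbumin and weight as primary, with BMI dropped or merged with weight. Apply Holm across them at 5% and state that any one significant result is success.

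Under either, adjust any arm contrasts used to interpret the primary outcome.

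**Cost.** This is more than a wording change. It amends a recruiting trial, must be reported to the ethics committee, and leaves fewer results that can be called primary. Holm also lowers power that is already limited: by the plan's own inputs, from about 53% at 0.05 to 35% at the first step with three outcomes, or 31% with four. The amendment should state that loss.

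### Table 2 measures change at 30 and 90 days from the pre-discharge visit while the text says baseline, and the pre-discharge value may already carry part of the treatment effect in comparisons with Group DS

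*Protocol article*

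**What the plan says.** All references are to the protocol article.

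- **Outcomes of the study {12}, text.** The changes are "assessed at a day prior to discharge (V3), 30 days after surgery (V4), and 90 days after surgery (V5) compared to baseline". The sentence points to Table 2 as showing this.
- **Outcomes of the study {12}, Table 2.** Baseline (V1) is the reference only for V3. For V4 the entry is "change from 1 day prior to discharge (V3) at 30 days after surgery (V4" and for V5 it is "change from 1 day prior to discharge (V3) at 90 days after surgery (V5". This metric covers all four primary outcomes (weight, BMI, albumin, prealbumin) and, as the table is laid out, the continuous secondary outcomes.
- **Statistical methods {20a}.** The primary model is stated as follows: "The primary analysis will employ repeated measures ANOVA (RMANOVA) to assess for time × group interactions". A secondary comparison uses "analysis of covariance (ANCOVA), controlling for baseline or at discharge values", and "ANCOVA will be restricted to per-protocol basis". Neither covariate is tied to a visit or to a pair of arms.
- **Explanation for the choice of comparators {6b}.** SS and SS-E are to take the supplement for 5 to 14 days before surgery; DS takes none before surgery. All three arms take it from surgery to discharge, and only SS-E continues afterwards.

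**The concern.** The text and the table give different reference points for the same outcomes at 30 and 90 days. They answer different questions. Change from V1 compares the arms on everything that has happened since randomisation. Change from V3 compares them only on what happens after the pre-discharge visit.

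For comparisons with DS the second is a poor measure of benefit. V3 is a post-randomisation value, taken after the arms were due different pre-operative treatment. If pre-operative supplementation works, some of its effect may be present at V3, and subtracting V3 subtracts that part. SS versus DS shows this most plainly: both arms stop the supplement at discharge, so V3-to-V5 change covers only the period after supplementation has ended. Adjusting for V3 in ANCOVA has a milder form of the same fault.

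Two definitions in force also leave room to choose between them once results are known, and the blinding section says the analysts will not be blinded.

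**Working it through.** **Inputs**

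- From the sample size section: a between-group albumin difference of 4 g/L and an SD of 6.5 g/L. They are borrowed only to set a scale.
- Assumed, because the article does not give them: equal mean and SD at V1, V3 and V5 apart from the treatment effect; a true arm difference at V5 of 4 g/L; an arm difference at V3 of 2 or 4 g/L; a between-visit correlation r of 0.3, 0.5 or 0.7.

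The plan states no figure for the V3 effect or for the bias, so there is none to reproduce.

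**Step 1: change scores.** Let e3 and e5 be the mean differences (SS or SS-E minus DS) at V3 and V5, with equal means at V1.

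- Change from V1: e5 − 0 = e5.
- Change from V3: e5 − e3.

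With e5 = 4, the V1 reference gives 4 whatever e3 is. The V3 reference gives 4 − 2 = 2 when e3 = 2, and 4 − 4 = 0 when e3 = 4. If instead the arms have converged by V5 (e5 = 0) after a V3 difference of 4, the V3 reference gives 0 − 4 = −4, an apparent advantage for DS where none exists at V5. Whenever 0 < e5 < e3, the sign is reversed.

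**Step 2: ANCOVA.** With equal SDs the within-arm slope of V5 on V3 is r. The adjusted difference is therefore e5 − r × e3. Adjusting for V1 gives e5 − r × 0 = e5.

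| r | V3 effect 2 g/L | V3 effect 4 g/L |
|---|---|---|
| 0.3 | 4 − 0.6 = 3.4 | 4 − 1.2 = 2.8 |
| 0.5 | 4 − 1.0 = 3.0 | 4 − 2.0 = 2.0 |
| 0.7 | 4 − 1.4 = 2.6 | 4 − 2.8 = 1.2 |

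**Step 3: check by simulation.** A large simulated sample (400,000 patients in two arms, SD 6.5) agreed. Change from V1 and ANCOVA on V1 both returned about 4.0. Change from V3 returned about 2.0 and 0.0. ANCOVA on V3 returned 3.40, 3.00 and 2.61 for a V3 effect of 2, and 2.83, 1.98 and 1.19 for a V3 effect of 4.

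**Step 4: which comparisons are affected.** SS and SS-E have the same planned treatment up to discharge, so the expected e3 between them is 0 and the V3 reference does not shift that comparison. The distortion applies to SS versus DS and SS-E versus DS.

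**Step 5: which analyses are affected.** The primary model tests a time × group interaction on repeated measurements. If all visits enter as raw values, that overall test is the same whichever visit is called the reference. The affected items are the Table 2 changes, the effect estimates reported from them, and the secondary ANCOVA if it uses the discharge value.

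**The case against.** The strongest reply is that Table 2 splits the follow-up into two phases on purpose: V1 to V3 for the peri-operative phase, and V3 onwards for the extended phase. The two add up to V1-to-V5 change, so the pre-operative effect is placed in another row and not lost. For SS-E versus SS this is a sensible measure of extended supplementation. That part stands, and the fix keeps it. But Table 2 does not confine the V3 reference to that pair of arms, it contains no direct V1-to-V4 or V1-to-V5 change, and on this reading the text of the section would still be wrong.

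Three further limits also stand.

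- A reader might infer that the trial's primary test is biased or could be reversed. The documents do not support that: the named primary analysis is the interaction test, which does not use a V3 change score. The article does not list the visits entered, but nothing suggests V3-anchored data.
- A reader might infer that supplementation has already changed the V3 value, or that adjusting for V3 removes the effect altogether. The article plans for such an effect but does not show one, and in the cases worked above ANCOVA attenuates the effect without cancelling it. The ANCOVA is also secondary and confined to the per-protocol set.
- The wording "controlling for baseline or at discharge values" does not say that the discharge value serves comparisons with DS at V4 and V5. This is the natural reading beside Table 2, but it is an inference, and an analysis plan not shown may settle it.

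**Conclusion.** The contradiction between the text and Table 2 is literal and concerns the definition of every primary outcome at 30 and 90 days. In comparisons with DS, the Table 2 version estimates e5 − e3 in place of e5, and can hide or reverse an effect at those visits. Its size equals whatever arm difference exists at V3, which is unknown. For an assumed V5 effect of 4 g/L, the reported change would be 2 g/L with a V3 effect of 2, and 0 with a V3 effect of 4. ANCOVA on V3 would give about 1.2 to 3.4 g/L over the assumed V3 effects of 2 to 4 g/L and correlations of 0.3 to 0.7. If e3 is 0 there is no bias, though the contradiction remains. The point is limited to the outcome definitions, the estimates built on them and the secondary ANCOVA.

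**What to change.** 1. In Table 2, define change at V3, V4 and V5 against V1, in line with the text of the section.
2. In the statistical methods, adjust the ANCOVA for the V1 value in every comparison that involves DS, and drop the open choice of covariate.
3. Keep V3-referenced change, or adjustment for V3, only as a labelled supplementary analysis of SS-E versus SS.

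No new data are needed, since V1 values are already collected. The trial is recruiting and Table 2 defines primary outcomes, so this is a protocol amendment to be reported to the ethics committee. It should be settled before any analysis.
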